# BACKGROUND

The major hurdle of COVID-19 is the early recognition of the patients at high risk for the development of severe respiratory failure (SRF). If this can be achieved early, then appropriate immunomodulatory treatment may be administered to prevent development of SRF. This scenario is extremely visionary since it prevents the development of the major fatal consequence of Covid-19 but also alleviates the heavy medical and financial burden of Intensive Care Unit (ICU) admission.

Current evidence suggests that SARS-CoV-2 activates endothelial function which leads to over-production of D-dimers^1,2^. uPAR (urokinase plasminogen activator receptor) is anchored to the cell membranes of the lung endothelial cells. As result of the activation of kallikrein, uPAR is cleaved and enters the systemic circulation as the soluble counterpart suPAR^3^. Preliminary unpublished data from 57 Greek patients hospitalized after March 1^st^ 2020 in Greek hospitals due to pneumonia by confirmed SARS-CoV-2 infection showed that those with suPAR admission levels ≥ 6 ng/ml had greater risk for the development of SRF within 14 days than patients with suPAR less than 6ng/ml (Figure 1). The sensitivity of suPAR to detect these patients was 85.9% and the positive predictive value 85.9%. It needs to be outscored that all 21 Greek patients with suPAR≥ 6ng/ml were under standard-of-care treatment, which at that moment consisted of hydroxychloroquine and azithromycin. These data were confirmed in 15 patients hospitalized for pneumonia by SARS-CoV-2 in Rush Medical Center at Chicago^4^. A recent publication of 881 patients from the ISIC database verified these results^5^.

This prognostic ability of suPAR for unfavourable outcome is not presented for the first time; in the TRIAGE III trial that was conducted among 4,420 admissions in the emergency department in Denmark the interquartile range of suPAR was between 2.6 and 4.7 ng/ml in 30-day survivors and between 6.7 and 11.8 ng/ml in 30-day non-survivors^6^. Previous data from the Hellenic Sepsis Study Group on 1,914 patients clearly shows a high prognostic utility of admission suPAR for 28-day mortality^7^.

[figure not shown]

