**STATISTICAL ANALYSIS PLAN (5 October 2020)**

The study is powered for the primary endpoint making the hypothesis that 60% of patients with lower respiratory tract infection due to COVID-19 and suPAR≥6 ng/ml upon hospital admission will develop SRF. To decrease this to 45% with power of 90% at a 5% level of significance, two hundred sixty (260) patients need to be enrolled. Taking into consideration, the single-arm study design, 500 patients should be enrolled to make results more robust. Data will be analyzed for the intention-to-treat (ITT) population.

An interim analysis will be conducted after completion of the 30-day follow up of the first 130 patients, i.e. 50% of the number of patients needed to be enrolled as calculated by power analysis. Parallel comparators receiving standard-of-care treatment (SOC) will be used all patients hospitalized at the same time period in eight departments of Internal Medicine in tertiary hospitals of Athens who were participating in the registry of the Hellenic Sepsis Study Group without participating in the SAVE trial ([www.sepsis.gr](http://www.sepsis.gr)). Data and biosample collection is done in the SOC comparators after written informed consent. The same inclusion and exclusion criteria will apply in the parallel comparators under SOC as in patients participating in the SAVE trial. Data collection in these departments has been approved by the Ethics Committees of the participating hospitals. Propensity matching will be performed among comparators to the 130 patients enrolled in the SAVE trial, so as the 130 comparators will be fully comparable to all below criteria:

- Age
- Comorbidities, as expressed by the Charlson’s Comorbidity Index
- Admission severity scores namely pneumonia severity index (PSI), acute physiology and chronic health evaluation (APACHE) II score, SOFA score and WHO severity classification of COVID-19
- Co-administered treatment of azithromycin, hydroxychloroquine and dexamethasone

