Primary outcome and binary secondary outcomes as well as serious adverse event and adverse event rates between the two groups will be expressed as percentages and will be compared by the Fisher exact test, calculating also the respective odds ratios. The time to an event will be compared between the two groups by survival analysis. Stepwise Cox regression analysis will be conducted for the primary outcome and 30-day mortality. Quantitative secondary outcomes will be expressed as median values with respective interquartile range and will be compared by the Mann-Whitney U test.

The cost of hospitalization will be measured by adding the itemized cost of stay, drugs, and interventions and will be expressed as median with respective interquartile range. Salaries of nurse and medical stuff will not be included. Cost comparison will be done by the Mann-Whitney U test.

Qualitative baseline characteristics will be expressed as frequencies and percentages and compared by the Fisher exact test. Quantitative baseline characteristics will be expressed as mean values with standard deviation if following a normal distribution or median values with quartiles if following linear distribution. Comparisons of quantitative baseline characteristics will be done by the Student’s t-test or by the Mann-Whitney U test respectively. Paired comparisons will be done by the Wilcoxon’s rank-signed test. Non-parametric correlations will be done according to Spearman.

Analysis will be conducted with SPSS Version 25.0. All P values will be two-sided. Any P value <0.05 will be considered as statistically significant.

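### Hospital cost is to be compared by medians and a rank test, which cannot give the cost or saving per patient and can point the wrong way if the drug price is a large share of the saving it produces

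*Supplement*

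**What the plan says.** The cost paragraph of the Statistical Analysis Plan (5 October 2020) defines the outcome: "The cost of hospitalization will be measured by adding the itemized cost of stay, drugs, and interventions". The total "will be expressed as median with respective interquartile range. Salaries of nurse and medical stuff will not be included". The test follows: "Cost comparison will be done by the Mann-Whitney U test". The SAP's general rules then apply: "All P values will be two-sided" and "Any P value <0.05 will be considered as statistically significant".

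The SAP does not name the groups for the cost comparison. The only two-group comparison it describes sets 130 SAVE patients against propensity-matched standard-of-care comparators, chosen "so as the 130 comparators will be fully comparable to all below criteria", and I assume that this is the one meant.

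Neither the SAP nor protocol version 3.0 plans a mean cost, a difference in mean cost, or an interval for either. Cost is not listed under Study Endpoints in the protocol. The protocol's one economic remark is in the Background, where preventing SRF "also alleviates the heavy medical and financial burden of Intensive Care Unit (ICU) admission".

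**The concern.** A total or per-patient cost is a mean. A mean multiplied by the number of patients gives expenditure; a median does not. The Mann-Whitney test asks whether a randomly chosen SAVE patient is as likely to cost more as to cost less than a randomly chosen comparator. It takes no account of how much more or less.

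The two questions can part company in this trial. Every SAVE patient is to receive anakinra, and drugs count towards cost, so the drug adds a roughly constant amount to every treated patient. The saving comes only from patients spared SRF: 15 in 100 on the SAP's planning rates, or 20 in 100 on the protocol's. Ranks register the added amount in everyone but discount the size of the saving in those few.

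At stake is the reading of one economic result: a significant P value could be reported as showing that anakinra is dearer when mean cost is equal or lower. The primary endpoint is not affected.

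**Working it through.** **Inputs from the documents.** 130 v 130; two-sided 0.05; SRF rates of 60% and 45% (SAP) or 55% and 35% (protocol, Number of Patients); drugs included in cost. There is no planned cost figure to reproduce.

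**Assumptions.** Relative units. A stay without SRF has mean 2 (CV 0.6). A stay with SRF has mean 6, 10 or 15 (CV 0.8). Both are lognormal. The drug adds a constant d to each SAVE patient.

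**Break-even price.** Mean costs are equal when d = (SRF rate in comparators − SRF rate in SAVE) × (SRF cost − non-SRF cost).

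| SRF rates | SRF cost | Break-even d | d ÷ ordinary stay of 2 |
|---|---|---|---|
| 55% to 35% | 6 | 0.20 × 4 = 0.80 | 40% |
| 55% to 35% | 10 | 0.20 × 8 = 1.60 | 80% |
| 55% to 35% | 15 | 0.20 × 13 = 2.60 | 130% |
| 60% to 45% | 6 | 0.15 × 4 = 0.60 | 30% |
| 60% to 45% | 10 | 0.15 × 8 = 1.20 | 60% |
| 60% to 45% | 15 | 0.15 × 13 = 1.95 | 97.5% |

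Check of the third row: comparators 0.55 × 15 + 0.45 × 2 = 9.15; SAVE 0.35 × 15 + 0.65 × 2 + 2.60 = 9.15.

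**Simulated chance of a significant result in the direction 'anakinra dearer'.** Ranges run over the three SRF costs; the choice of random seed moves them by a few percentage points.

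| Drug price | Mann-Whitney, 55% to 35% | Mann-Whitney, 60% to 45% | Welch test of means |
|---|---|---|---|
| Break-even (equal means) | about 32–65% | about 15–34% | about 2–4% |
| 80% of the saving (SAVE truly cheaper) | about 13–39% | about 7–19% | about 1% |
| 5–10% of an ordinary stay | at most 0.3% | at most 0.3% | – |

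**Check on a second cost scale.** Here a non-SRF stay has mean 1, an SRF stay mean 3, 5 or 10, and the CV is 0.3, 0.6 or 1.0. At break-even 'dearer' occurs in about 14–74% of trials (55% to 35%) or 7–52% (60% to 45%), against 1.8–3.0% by Welch.

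One cell can be checked by hand: 55% to 35%, SRF cost 5, CV 0.6.
- Comparator mean: 0.55 × 5 + 0.45 × 1 = 3.20.
- Break-even d: 0.20 × 4 = 0.80. SAVE mean: 0.35 × 5 + 0.65 × 1 + 0.80 = 3.20.
- The simulated probability that a SAVE patient costs more than a comparator is 0.552.
- The null standard error of that probability is √[(2n+1)/(12n²)] = √[261/202,800] = 0.0359.
- The shift is 0.052/0.0359 = 1.45, so the chance of exceeding 1.96 is 1 − Φ(0.51) ≈ 31%. Simulation gives 32%, against 2.7% by Welch.

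More patients make it worse, because the test is answering a different question accurately: the same cell gives 55% at 250 v 250.

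**Power to show a true saving.** This can go either way. First cost scale, Mann-Whitney v Welch:
- Drug at 5% of an ordinary stay: 35 v 32%, 59 v 47% and 67 v 50% (55% to 35%; SRF cost 6, 10, 15); 20 v 16%, 38 v 26% and 41 v 28% (60% to 45%).
- Drug at 10% of a stay: Mann-Whitney is higher in four of the six settings.
- Drug at 20% of a stay: Mann-Whitney has less power, though 'dearer' is still at most 3.3%.
- Drug at 50% of a stay (d = 1.0, SRF cost 15, 55% to 35%; mean cost 9.15 v 7.55, a 17% saving): 3 v 26%.

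**The case against.** The strongest objection is that the alarming rates need a dear drug. The documents give no price, and break-even in the first model means a drug costing 30–130% of an ordinary stay. With a cheap drug the rank test points the right way, often with more power than a comparison of means. This stands. A reader might infer that Mann-Whitney generally loses power to show a saving, or that even a small added cost per patient would mislead it. The documents do not support either reading, and the low-price results contradict both.

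Second, cost is not a stated objective. A reader might infer from the Background that the protocol poses a budget question which the SAP then fails to answer. The Background remark is one sentence of rationale; cost is absent from the aim and from the primary and secondary endpoints. This also stands, and it lowers the priority.

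Third, costs are skewed, and the median with a rank test is the SAP's own rule for quantitative secondary outcomes. That explains the choice but does not answer the point. Skewness is a reason to take care over the interval for a mean, for example by bootstrap; it does not turn a rank test into a statement about cost per patient. Under the skewed costs assumed here, the Welch test stayed close to its nominal level at 130 per group.

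Nor is the comparison purely descriptive: the SAP plans a test, and its 0.05 rule covers it.

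**Conclusion.** The concern holds in a limited form. What is certain from the text is that the planned cost analysis yields no mean cost, no difference in mean cost and no interval, so it cannot give the cost or saving per patient.

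What is conditional is the wrong-direction result. It can occur often when the drug price is a large share of the saving it produces, and it practically vanishes when the drug costs 5–10% of an ordinary stay. All the percentages rest on assumed cost ratios, lognormal spread, a constant drug cost and 130 per group. They show that the rank test and the mean can disagree; they do not predict that they will in this trial. The results therefore do not support a claim that anakinra would be wrongly found dearer.

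Because cost is an SAP-only outcome in a non-randomised comparison, this is a point to consider rather than a required change.

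**What to change.** In the cost paragraph of the SAP, make the comparison the difference in arithmetic mean cost per patient (SAVE minus comparators) with a 95% bootstrap confidence interval, resampling matched pairs where matching is used. Keep the median and interquartile range as description. If a Mann-Whitney P value is still shown, state that it compares rank ordering and is not evidence on cost per patient. Name the groups compared, and repeat beside the result that staff salaries are excluded.

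This costs a sentence or two in the SAP and a short bootstrap, with no new data. The downside is that the interval for a mean of skewed costs is wide and may be inconclusive.

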# LABORATORY PROCEDURES

Blood samples will be collected in EDTA-coated and not-EDTA-coated tubes and in PAXgene tubes. Samples will be transferred on the day of collection to the central Lab, which is the the Laboratory of Immunology of Infections at the 4^th^ Department of Internal Medicine at ATTIKON University General Hospital. Analysis will be performed in the central Lab and in another European university Lab outside Greece.

Mediators of inflammation and suPAR will be measured in plasma and serum. Among measured mediators will be sIL-2R, IL-8 triglycerides as well as coagulation and fibrinolysis mediators.

All stored PAXgene tubes will be subjected to transcriptomic analysis. Part of the collected plasma will be stored at -80^o^C for proteomic and metabolomic analysis. Peripheral Blooed Mononuclear Cells (PBMCs) will be isolated after gradient centrifugation of whole blood over Ficoll. After serial washing, counting and exclusion of dead cells, they will be stimulated with purified ligands of SARS-CoV-2 for the production of TNFα, IL-1β, IL-6, ΙL-10, IL-17, IL-22 and IFNγ.

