## Secondary study endpoints

- Comparison of the primary endpoint with comparators receiving standard-of-care treatment
- Change of scoring for respiratory symptoms between days 1 and 7
- Change of scoring for respiratory symptoms between days 1 and 14
- Change of SOFA score between days 1 and 7
- Change of SOFA score between days 1 and 14
- Change of Peripheral Blood Mononuclear Cells’ (PBMCs) functionality between days 1 and 7
- Change of gene expression between days 1 and 7 (transcriptional, proteomic and metabolomic analysis)
- Change of plasma inflammatory mediators between days 1 and 7
- 30-day mortality
- 90-day mortality

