# INTERIM AND STATISTICAL ANALYSIS

An interim analysis will be conducted after completion of the 30-day follow up of the first 130 patients, i.e. 50% of the number of patients needed to be enrolled as calculated by power analysis. As comparators will be used patients hospitalized with pneumonia by the SARS-CoV-2 virus in other departments of Greek hospitals in which full data collection is performed by the Hellenic Sepsis Study Group, after written informed consent. Data collection in these departments has been approved by the Ethics Committees of the respective hospitals. For the purpose of this analysis, patients receiving standard-of-care treatment (SOC) will be selected among the total patients whose data are fully collected in order to fulfill the same inclusion and exclusion criteria as patients enrolled in the SAVE trial. Propensity matching will be performed among comparators and 130 patients enrolled in the SAVE trial, so as the 130 comparators will be fully comparable to all below criteria:

- Age
- Comorbidities, as expressed by the Charlson’s Comorbidity Index
- Admission severity scores namely pneumonia severity index (PSI), acute physiology and chronic health evaluation (APACHE) II score, SOFA score and WHO severity classification of COVID-19
- Co-administered treatment, such as azithromycin and dexamethasone

The primary endpoint will expressed as percentage and 95% confidence intervals. Comparisons with historical cases will be done by the Fisher exact test. Any p-value below 0.05 will be considered significant.

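### The unadjusted P<0.05 rule has no exception for the transcriptomic, proteomic and metabolomic endpoint, so about 5% of unchanged features tested under it would be declared changed

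*Supplement*

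**What the plan says.** **Threshold.** The last paragraph of the SAP (5 October 2020) sets "All P values will be two-sided" and then "Any P value <0.05 will be considered as statistically significant". Protocol version 3.0, under Interim and Statistical Analysis, has the same rule: "Any p-value below 0.05 will be considered significant". Neither statement has an exception.

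**Endpoint.** The Secondary study endpoints section of protocol version 3.0 and its synopsis both list "Change of gene expression between days 1 and 7 (transcriptional, proteomic and metabolomic analysis". Neither place marks this endpoint as exploratory or descriptive.

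**Assays.** Laboratory Procedures states "All stored PAXgene tubes will be subjected to transcriptomic analysis", and says that part of the plasma is frozen for "proteomic and metabolomic analysis". It gives no number of transcripts, proteins or metabolites, and names no platform or panel.

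**Tests.** The SAP does not mention the omics analyses by name. Two general sentences could reach them: "Quantitative secondary outcomes will be expressed as median values with respective interquartile range and will be compared by the Mann-Whitney U test" and "Paired comparisons will be done by the Wilcoxon’s rank-signed test". Neither comes with an adjustment, and neither current document mentions multiplicity or a false discovery rate.

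**The concern.** A 0.05 threshold is set for a single hypothesis. The omics endpoint is one line in the endpoint list, but it covers three platforms, each measuring many features at once. If every feature is tested and each P value below 0.05 is called significant, a fixed fraction of the unchanged features enters the list of changed ones, whatever the drug does, however many patients are sampled and whichever valid test is used.

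This differs from the debatable question of adjusting across the listed secondary endpoints. There are ten of those, seven clinical and three laboratory-based. Here the multiplicity lies inside a single listed endpoint, and the conclusion sought is which features changed. An unadjusted per-feature threshold puts no limit on the share of that list that is false. At stake is whether the trial's mechanistic findings can be reproduced.

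**Working it through.** **Inputs from the documents.** The threshold is 0.05 two-sided for any P value (SAP, last paragraph; protocol, Interim and Statistical Analysis). One listed secondary endpoint covers three platforms, day 1 against day 7. The plan states no expected number of false findings, so there is no figure of its own to reproduce.

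**Inputs assumed.** Each feature gets its own test. The number of features m is not given, so it is varied from 100 to 20,000.

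**Step 1: expected false findings.** With m0 truly unchanged features, the expected number declared changed is m0 × 0.05. The table takes all m features as unchanged (m0 = m). The 95% range is from a Binomial(m, 0.05), which treats features as independent; the expectation itself does not need independence.

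| Unchanged features | Expected false findings | 95% range |
| --- | --- | --- |
| 100 | 5 | 1 to 10 |
| 500 | 25 | 16 to 35 |
| 1,000 | 50 | 37 to 64 |
| 2,000 | 100 | 81 to 120 |
| 5,000 | 250 | 220 to 281 |
| 10,000 | 500 | 458 to 543 |
| 20,000 | 1,000 | 940 to 1,061 |

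If only half the features are unchanged, the count halves: 5,000 features give 0.5 × 5,000 × 0.05 = 125, and 20,000 give 500.

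**Step 2: how many features make the count large.** An expected count of 100 needs 100 / 0.05 = 2,000 unchanged features, and 200 needs 200 / 0.05 = 4,000.

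**Step 3: small panels.** The chance of at least one false finding is 1 − 0.95^m under independence. For m = 100 it is 99.4%.

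**Step 4: share of the list that is false.** Let p be the proportion of features unchanged. Assume 80% power for each truly changed feature (not in the documents). The false share is approximately 0.05p / [0.05p + 0.80(1 − p)].

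- p = 0.50: 0.025 / (0.025 + 0.400) = 6%
- p = 0.90: 0.045 / (0.045 + 0.080) = 36%
- p = 0.99: 0.0495 / (0.0495 + 0.0080) = 86%

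The share passes one half when 0.05p > 0.80(1 − p), that is when p > 0.80 / 0.85 = 0.94.

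**Step 5: with the fix.** Benjamini-Hochberg at 5% within a platform holds the expected false share of that platform's declared features at or below 5%, under its usual conditions (independent or positively dependent tests). It does not need m to be fixed in advance.

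**The case against.** The strongest reply is that this is an omission and not a wrong rule. The SAP never names the omics analyses. Its threshold closes a description of clinical, safety, cost and baseline comparisons run in SPSS, and Laboratory Procedures sends part of the laboratory analysis to a second university laboratory outside Greece. The omics data may well be analysed there by specialists who control the false discovery rate as routine.

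Part of this stands. The rule reaches the omics endpoint only through its general wording, and per-feature testing is an inference. A reader might infer that the plan prescribes thousands of paired Wilcoxon tests. It does not: no test is assigned to these data and no feature count is given.

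The reply does not remove the point. The endpoint is a listed secondary one, the threshold covers any P value, and nothing else in either document governs these data. If the intended practice is to control the false discovery rate, it contradicts the written rule and the SAP should say so. Leaving the threshold open until the data are seen allows it to be chosen by result.

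A second fair objection is that a near-global null is unlikely between day 1 and day 7 of acute COVID-19 pneumonia, where many features may truly change. This also stands, and it limits what can be said about the composition of the list.

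**Conclusion.** The point holds as a gap with a predictable consequence. The only significance rule in the plan is unadjusted and has no exception, and it covers a listed high-dimensional endpoint. If features are tested one by one under it, about 5% of the unchanged ones will be declared changed. The count rests on the assumed number of unchanged features: about 5 for 100, 50 for 1,000, 250 for 5,000 and 1,000 for 20,000.

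Two stronger readings are tempting and are not supported:

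- A reader might infer that the rule will produce hundreds of false findings. That needs roughly 2,000 to 4,000 or more unchanged features, and the documents give no count. Panels of 100 to 1,000 would give about 5 to 50.
- A reader might infer that the resulting list will be mostly false. At an assumed 80% power per feature, that needs about 94% or more of features to be unchanged. The documents support only that the false share could be large and is uncontrolled.

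The primary endpoint, the clinical secondary endpoints and safety are not affected. The change should be made, but the trial's main conclusion does not depend on it.

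**What to change.** Add one sentence to the SAP beside the significance rule: for the transcriptomic, proteomic and metabolomic endpoints, the false discovery rate is controlled at 5% by the Benjamini-Hochberg procedure within each platform, and the unadjusted 0.05 rule does not apply to them.

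This needs no new data, patients or assays and leaves all other analyses unchanged. The cost is that fewer features will be declared significant. The change limits chance findings only: a day 1 to day 7 change within treated patients can reflect the course of the disease as well as anakinra, and no error-rate control separates the two.
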